**Figure 2 figure2:**
[figure not shown]
Presentation of the overall solution. In this configuration, the solution comprises 4 passive infrared sensors to monitor activity (bedroom, kitchen, living room, and entrance hall); 1 contact sensor on the main entrance door; 1 cookie sensor on the fridge to monitor door opening; a pendant (or wristband) with a push-button emergency alarm; and a live intercom system (device in the left of the illustration) for direct audio communication with the support center (calling function).

The following data will be monitored: presence (yes/no) in specific rooms, for example, rooms associated with eating, bathing, and sleeping; time spent outdoors; total activity inside the home (estimated by the average number of sensor activations per day) [6]; fridge use; and sleeping patterns.

The solution can trigger 2 different types of alerts. The first consists of *conventional alerts*. They are generated by the participants using an alarm push button or through the intercom system. The second type of alert assessed in this project is automatically triggered by our artificial intelligence algorithm after an initial learning phase (eg, gradual change in sleeping pattern). The sensor-based alerts and the use of the Live intercom calling function are both directed to a telecare worker on a nationwide telecare platform (IMA/Serena) all 7 days a week and 24 hours a day. The telecare worker can suggest a range of actions, from direct contact with the older individual to a phone call to the care partner or to emergency services. The first month is dedicated to algorithm learning: all sensors are functional, but no automatic alert is generated from the platform. Activity data relating to sleeping, eating, and time spent outdoors, and so on, are recorded and analyzed. After the first month, there will be sufficient data to detect unusual behaviors and eventfully trigger an alert. The algorithm used to perform real-time detection of behavioral anomalies is described elsewhere [14].

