### Follow-Up Procedure

The first 5 participants are enrolled for a total of 10 months (an initial 4-month period followed by a 6-month follow-up period) and the other 20 participants for 6 months. An installation visit will take place in the days following enrollment. A remote follow-up evaluation will be carried out over the phone by a CRA every 2 months after the baseline assessment (see Table 2). The last visit will be conducted by the CRA in the participant’s home after 6 months. For the first 5 participants enrolled in the study, the baseline for data analysis is defined as the beginning of the 6-month follow-up period at the end of the first preliminary 4-month period which is dedicated to technical feasibility. The proper regulatory and ethical conduct of the study is monitored by a clinical research technician, acting on behalf of the University Hospital.

**Table 2 table2:** Data collection.

Variables	Preinclusion (CRA^a^, in-person)	Baseline T0 (investigator)	T2 months (CRA, phone)	T4 months (CRA, phone)	T6 months (CRA, in-home visit)
Informed consent	✓	✓	—^b^	—	—
Sociodemographic data	—	✓	—	—	—
ADL^c^, IADL^d^, MMSE^e^	—	✓	—	—	✓
Frailty criteria, SPPB^f^	—	✓	—	—	✓
Acceptability questionnaire, EQ5D^g^	—	✓	✓	✓	✓
Major medical events	—	✓	✓	✓	✓
Sensor data	—	Continuous measures	Continuous measures	Continuous measures	Continuous measures

^a^CRA: clinical research assistant.

^b^Data not collected.

^c^ADL: activities of daily living.

^d^IADL: instrumental activities of daily living.

^e^MMSE: mini mental state evaluation.

^f^SPPB: short physical performance battery.

^g^EQ5D-3L: EuroQol 5D score to describe and value health, quality of life questionnaire.

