### Statistical Analysis

The main analysis will be an intent-to-treat analysis. The quantitative outcomes will be estimated with 95% CI. Quantitative variables will be expressed by mean values and standard deviations. The 6-month follow-up period for the 25 participants will allow us to record the number and frequency of alerts generated by the solution. A total of 3 positive predictive value (PPV) calculations (estimation of legitimate alerts) will be done (95% CI, thanks to end users’ feedback for the overall follow-up period and for each 2-month follow-up period: 0-2 months, 2-4 months, and 4-6 months) to estimate the progression of algorithm performance. For the secondary objective, we will also analyze these 3 periods to evaluate the performance of the automatic alerts in detecting changes in functional or cognitive autonomy or major events (sensitivity, specificity, predictive value, and receiver operating characteristic [ROC] curves). Alerts will be addressed with both a binary approach (no alert vs 1 alert to estimate sensibility, specificity, PPV, and negative predictive value) and a continuous approach (number of alerts over the period to plot an ROC graph and estimate the area-under-the-curve). The Department of Epidemiology at our University Hospital will conduct statistical analyses using SAS version 9.4 (SAS Institute, Inc).

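### The secondary analysis scores raw alert counts per 2-month period, although automatic alerts are off in the first month, so first-period accuracy and the trend over periods partly reflect exposure

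*Protocol article*

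**What the plan says.** The Statistical Analysis section of the protocol article sets two scores for the secondary objective, which concerns how well automatic alerts detect functional or cognitive change or major events. The ROC score is the "number of alerts over the period to plot an ROC graph". The binary test is "no alert vs 1 alert to estimate sensibility, specificity, PPV, and negative predictive value". Both are applied to the three periods that the primary PPV uses: "for each 2-month follow-up period: 0-2 months, 2-4 months, and 4-6 months". Neither score has a time denominator. The section says that the frequency of alerts will be recorded, but does not carry it into either score.

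The Procedure section (text under Figure 2) says of the first month that "all sensors are functional, but no automatic alert is generated from the platform".

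The Follow-Up Procedure section says: "The first 5 participants are enrolled for a total of 10 months". For them, "the baseline for data analysis is defined as the beginning of the 6-month follow-up period at the end of the first preliminary 4-month period".

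The Study Measures section defines a major medical event as one that leads to a physician or paramedic attending at home, or to an emergency call. These events are collected in retrospect, by phone, every 2 months.

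**The concern.** A count over a fixed calendar period is a fair index test only if everyone could generate alerts for the same time. Here the period 0-2 months includes the learning month for the 20 later participants. The first 5 appear to have done their learning before their month 0.

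Three things follow within the plan as written. The first-period score partly ranks participants by enrolment phase. An event in the alert-free month cannot have been flagged when it happened. It is scored as missed, unless an alert in month 2 turns it into a hit by chance. And the periods are compared to see how performance develops, while live time rises sharply between the first period and the second.

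The Discussion says that these results are meant to inform the sample size of a future study, so a distortion here would carry into that calculation.

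**Working it through.** **Inputs.** 25 participants, 5 with a preliminary phase and 20 without (Follow-Up Procedure). No automatic alerts in month 1 (Procedure). 2 alerts per participant over 6 months (the example in Sample Size). Poisson counts are my assumption.

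**1. The plan's own figure.** 25 × 2 = 50 alerts, 25 of them valid. The exact binomial 95% CI is 35.5% to 64.5%, as stated. The article gives no figure for the secondary analysis, so the steps below are illustrations.

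**2. Live time.**
- 0-2 months: 20 × 1 + 5 × 2 = 30 person-months, if the first 5 did not relearn.
- 2-4 and 4-6 months: 25 × 2 = 50 person-months each.

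**3. Chance of at least one alert.** P = 1 − exp(−λt), with λ = 2/6 = 1/3 per month.
- 1 live month: 1 − exp(−0.333) = 28%.
- 2 live months: 1 − exp(−0.667) = 49%.
- All participants, 0-2 months: (20 × 0.283 + 5 × 0.487)/25 = 32%.
- All participants, later periods: 49%.

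**4. Effect on accuracy.** Take an algorithm that alerts twice as often in participants with an event (assumed ratio), and ignore when in the period the event occurs.
- Sensitivity, later periods: 1 − exp(−1.333) = 74%.
- Sensitivity, 0-2 months: (20 × 0.487 + 5 × 0.736)/25 = 54%.
- Specificity, later periods: 1 − 0.487 = 51%.
- Specificity, 0-2 months: 1 − 0.324 = 68%.

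The algorithm is the same throughout. Only live time has changed.

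**5. Other assumptions.**
- Spread the 50 alerts over the 30 + 50 + 50 = 130 live person-months: λ = 0.385, giving 32% v 54% by enrolment phase, and (20 × 0.319 + 5 × 0.537)/25 = 36% in 0-2 months v 54% later.
- 1 alert per month (assumed upper case): 63% v 86% by phase, and (20 × 0.632 + 5 × 0.865)/25 = 68% v 86% later.
- If the first 5 did relearn: 25 × 1 = 25 person-months in 0-2 months, and 28% v 49% later. The contrast between phases disappears, but the contrast between periods grows.

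**6. Ranking by phase.** AUC = P(X > Y) + ½P(X = Y). With Poisson means 0.667 (first 5) and 0.333 (others), AUC = 0.61 although the underlying rates are equal.

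**7. Absence after an event.** The article does not say how alerts behave while a participant is away. If none fire, and every event participant is away for the stated time (both assumed), the null AUC at λ = 1/3 is 0.48 for 1 week, 0.45 for 2 weeks, 0.43 for 3 weeks and 0.39 for 1 month. If only 20% to 50% of event participants are away for 3 weeks, it is 0.8 × 0.50 + 0.2 × 0.425 = 0.49 to 0.5 × 0.50 + 0.5 × 0.425 = 0.46.

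**8. Would a rate cure it?** Not by itself. With alerts per live day and no true signal, the AUC is 0.54 for 1 week away, 0.48 for 3 weeks and 0.45 for 1 month. First 5 against the others, it is 0.55. At low counts, zeros stay tied and the non-zero rates fall on different steps. With equal live windows and equal rates, the two distributions are identical and the AUC is 0.50.

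**The case against.** A reader might infer more: that participants hospitalised for an event score low because they are away, so that AUC and sensitivity are biased downward. The article does not support this. Its definition of a major event does not name admission, and many qualifying events are dealt with at home. It gives no lengths of stay and no rule for suspending alerts. Time outdoors and in-home activity are monitored, so absence or stillness could itself trigger an alert. The direction is unknown, and the figures in step 7 are conditional.

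The AUC of 0.61 in step 6 also needs care. It separates enrolment phases, which nobody plans to estimate, and it would shift the event AUC systematically only if phase and outcome were associated. The first 5 may have relearned too, because the preliminary phase exists to allow changes to the system. Both points stand, but neither removes the contrast between periods in steps 3 to 5.

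The strongest general objection is that person-time is a detail for the full protocol or SAP, and that this is a secondary analysis in 25 people which the authors already expect to be limited. The second half is a fair reason to keep the point in proportion. The first half does not answer it: the article does not leave the score open, but fixes it as a count or as any alert within a calendar period that includes an alert-free month.

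**Conclusion.** The point holds for the secondary sensitivity, specificity, predictive value and ROC analyses. Followed as written, the share of participants with an alert rises from about 32% in 0-2 months to 49% later, at the example rate and with no change in the algorithm. First-period sensitivity is lowered and specificity raised by construction, events in the learning month could not have been flagged, and improvement after the first period cannot be told apart from added live time.

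The alert-free month and the three periods are documented. The percentages rest on the example alert rate, Poisson counts, full follow-up and no relearning by the first 5. Other choices in step 5 change the size but not the direction. Absence after an event is a possible further bias of unknown sign.

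The primary PPV has alerts as its denominator. Less live time makes it less precise in the first period, but does not bias it by this mechanism. The change should be made, but the primary result does not depend on it.

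**What to change.** For the secondary sensitivity, specificity and ROC analyses:

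- Exclude alert-free learning days and the events that fall in them.
- Compare participants and periods over windows with the same number of live days. One way is to use month 2 only in the first period, and one-month windows in the later periods for the comparison.
- State whether the first 5 participants relearned at their month 0.
- Report live days per period beside each estimate.
- State how alerts generated while the participant is away are counted, and treat documented absence in a sensitivity analysis.
- Do not rely on alerts per day alone (step 8).

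The cost is one derived variable for live days, from sensor data already collected continuously. Event dates and dates of absence are also needed. The article does not say that these are recorded, so they may have to be added to the 2-monthly phone call. The statistical price is fewer alerts and events in the first period, and so wider intervals there.

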## Results

The trial was registered with ClinicalTrials.gov (NCT03484156) on March 30, 2018. The enrollment process is spread out to allow for changes to the system in the event of technical problems.

The first phase with 5 participants (4-month feasibility period) has been completed and the expected completion date for the second phase of the study (20 participants for 6 months) is July 2020.

## Discussion

### Strengths and Limitations of Our Study

Older adults express the desire to live autonomously in their own homes. Clinicians, on the other hand, have difficulty monitoring the functional and cognitive autonomy of seniors over time because of the limitations associated with in-person measurements and self-reported data [5]. To date, despite the rapid pace at which research projects and commercial electronic health devices are developing, few solutions really meet these daily needs. We believe that, following a learning phase, our low-cost unobtrusive solution could trigger alerts if the sensors were to detect an acute, unusual event or a subtle change in everyday habits over time. This solution could provide relevant information to care partners and health professionals to support patient follow-up. The originality of our real-life project lies in the choice of the primary outcome and in our user-centered evaluation rather than in the technical specifications. We will evaluate the relevance of the alerts according to the end users and the progression of our algorithm performance over time. One of the main obstacles to the wide dissemination of alert systems is the low acceptability to end users (eg, false positive alarms) and the difficulty of integrating this approach into a complex and overburdened health care system. In our study, the primary endpoint is determined by the end users themselves. We strive to go beyond traditional medical event considerations such as severe falls, minor falls and minor events, and major events, which do not always make sense for older people. The strengths of our monitoring and support solution can be summarized in several points: it meets the needs of older people living alone; it includes an end user assessment; it is a nonintrusive solution; we use inexpensive sensors without heavy maintenance; and finally, the learning algorithm should increase the solution’s performance over time based on the end user feedback.

Concerning the potential limitations, we plan to analyze the performance of automatic alerts in detecting major events and changes in participants' autonomy (to calculate the number of subjects to be included for a future study). Although our population is at high risk, it is likely that the duration of follow-up is insufficient, particularly for autonomy loss. However, our center implements other studies in comparable populations on which we can rely for such a sample size calculation.

### Our Study in the Context of Previous Research

Several products on the market propose comparable monitoring solutions with very similar technologies [20-22]. However, we were unable to find objective evaluation reports supporting their advertised performance. A review of technologies for monitoring seniors’ home activities identified 5 main types of promising surveillance technologies: PIR motion detectors, worn body detectors, pressure sensors, video surveillance, and sound recognition. This area of research is not totally mature, and most studies did not take place in real-life settings [23]. In a previous study, Franco et al obtained interesting results by recording the electrical activity of 13 subjects monitored for a period of 6 months [24]. The results highlighted the possibility of differentiating between daily and nocturnal activities, and of calculating the probability of having eaten, bathed, or used the toilet with acceptable accuracy. Another study, conducted by Stucki et al, evaluated a nonintrusive, assistive technology system that recognizes and classifies ADL, thanks to passive sensors in each room (20 days, 10 healthy participants, mean age 49 years) with good sensitivity and specificity [25]. Urwyler et al also investigated the behavior of 20 participants using an unobtrusive wireless sensor network for 20 consecutive days. Differences in ADL regimens were significant between healthy controls and patients with dementia [26]. Few academic studies addressed the specific everyday needs of older adults and their families using such a *bottom-up* approach. We think that our study complements previous works.

### Conclusions and Perspectives

Our project brings together partners from the fields of health, technology, industry, and health insurance to develop a relevant but also economically sustainable solution. This is an opportunity for each partner to test the option of integrating such an innovative network into its current practices. Retrospective correlations will be used in this longitudinal study, which justifies further research to prospectively demonstrate the true predictive value of our algorithm.

## Abbreviations

ADL: activities of daily living
CRA: clinical research assistant
MMSE: mini mental state evaluation
PIR: passive infrared
PPV: positive predictive value
ROC: receiver operating characteristic
